#### Primary outcome analysis

The main analysis will follow a prespecified intention-to-treat statistical analysis plan, which will be finalized and preregistered prior to unblinding. The primary outcome variable is the BDD-YBOCS-A total severity score at the primary endpoint (1-month follow-up). All the randomized participants will be included in a linear mixed-effect model to estimate the difference between group means over time. Linear mixed models use all available data, can properly account for correlation between repeated measurements on the same subject, have greater flexibility to model time effects, and can handle missing data. The model will include fixed effects of time (baseline, post-treatment, and 1-month follow-up), treatment group (ICBT or IRT), site (Region Stockholm, Västra Götalandsregionen, or Region Skåne), and interaction effects of group by time, group by site, site by time, and group by site by time, as well as random intercept to account for individual differences. If the effects of site are not statistically significant, this variable will be dropped from the model to obtain a more parsimonious model. The primary source of inference will be the between-group difference at the primary endpoint (1-month follow-up), estimated from the group by time interaction. Additionally, between-group effect sizes will be estimated using Cohen’s *d*.

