### Participants

#### Eligibility criteria

The inclusion criteria for participation are (1) a primary diagnosis of BDD, based on the 5th edition of the Diagnostic and Statistical Manual of Mental Disorders (DSM-5) [32]; (2) a total BDD symptom severity score ≥24 on the Yale-Brown Obsessive-Compulsive Scale Modified for Body Dysmorphic Disorder, Adolescent version (BDD-YBOCS-A); (3) age between 12 and 17 years; (4) a minimum of one available parent/caregiver able to co-participate and support the adolescent throughout the treatment; and (5) regular access to a computer connected to the Internet and a mobile phone to receive text messages.

The exclusion criteria are (1) previous CBT for BDD for a minimum of five sessions with a qualified therapist within the 12 months prior to the inclusion assessment; (2) simultaneous psychological treatment for BDD or for any psychiatric comorbidity; (3) initiation, change of dosage, or cessation of any selective serotonin reuptake inhibitors (SSRIs) or antipsychotic drugs within the 6 weeks prior to the inclusion assessment; (4) a diagnosis of organic brain disorder, intellectual disability, psychosis, bipolar disorder, eating disorder, severe depression, or alcohol/substance dependence; (5) immediate risk to self or others requiring urgent medical attention or inpatient care, such as suicidality, or repeated self-injurious behaviors; (6) a documented suicide attempt in the last 12 months; (7) adolescent and parent/caregiver not able to read and communicate in Swedish; or (8) having a close relationship to an already included participant (e.g., sibling, cousin), to avoid being randomized into two different arms, with the risk of information “leaking” between the groups.

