### Power analysis

Between-group effect sizes in an RCT comparing face-to-face CBT with an active control in youth with BDD [5] and an RCT comparing ICBT with an active control in adults with BDD [26] were *d* = 1.13 and *d* = 0.94, respectively. Other pediatric ICBT trials similar to ours have reported smaller effect sizes. For example, an ICBT study of adolescent OCD [58] and an ICBT study of adolescent social anxiety disorder [59] reported between-group effect sizes of *d* = 0.69 and *d* = 0.64, respectively. Similarly, an adult BDD trial with an active control condition reported an effect size of *d* = 0.76 [60]. Thus, we have powered our study to be able to detect at least a moderate effect size of *d* = 0.50. A sample size of 128 participants was calculated to be sufficient with a power of 80%, with a 2-tailed *α* = 0.05. An additional 20% of participants will be added to account for potential dropouts. Hence, we aim to recruit a total of 154 participants (77 per group).

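### The primary model names only a random intercept across three unevenly spaced visits; if post-treatment and 1-month scores correlate more strongly with each other than with baseline, the nominal 5% test could run at about 6-10%

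*Protocol article*

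**What the plan says.** The section on primary outcome analysis lists the model terms: time (baseline, post-treatment, 1 month), group, site, all their interactions, "as well as random intercept to account for individual differences". It names no random slope, residual structure or robust standard error. The primary inference is the group difference at 1 month, obtained from the group-by-time interaction. The same section says of linear mixed models in general that they "can properly account for correlation between repeated measurements on the same subject".

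The section on secondary outcomes carries this framework over to the secondary variables. The long-term follow-up section also uses a random intercept, for 1, 3 and 6 months and without a group term.

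The power analysis sets the test "with a 2-tailed *α* = 0.05". The opening of the statistical analysis section says that the full analysis plan takes precedence where it differs, and that it will be finalised before the last participant reaches the primary endpoint.

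**The concern.** A random intercept with independent residuals is compound symmetry: one variance for all three visits and one correlation for all three pairs. The design gives two reasons to doubt equal correlations.

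- **Spacing and treatment.** Baseline and post-treatment are up to 14 weeks of guided treatment apart. Post-treatment and the primary endpoint are about one month apart, without therapist support and before crossover is offered.
- **Raters.** Site clinicians do the inclusion assessments; external blinded assessors do the later ones.

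Both suggest that post-treatment and 1-month scores correlate more strongly with each other than either does with baseline. The model would then average the small post-to-1-month difference variance into its residual and use the result for the baseline-to-1-month contrast. The confidence interval would be too narrow and the false-positive rate of the trial's one primary test would exceed its stated level.

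**Working it through.** **The plan's own figure.** The sample size is for "at least a moderate effect size of *d* = 0.50" with 80% power at two-sided 0.05. A two-sample t-test needs 63.8, so 64 per arm or 128 in total (power 0.801). Adding 20% gives 128 × 1.20 = 153.6, so 154. The stated figures reproduce. This calculation uses no between-visit covariance, so it does not inform the question here.

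**Inputs.** From the article: alpha 0.05 two-sided, 77 per arm, three visits, random intercept only. Assumed, because the article gives none: the SD at each visit and the three correlations, written below in the order baseline/post, baseline/1 month, post/1 month.

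**Formulas (large sample, complete data, no site terms).** Let D be the variance of the difference between two visits: D = SDi² + SDj² − 2·r·SDi·SDj.

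- Change contrast (baseline to 1 month, group by time): the random-intercept model in effect uses the mean of the three D values, where the correct value is D(baseline, 1 month). SE ratio = √(mean D / D(baseline, 1 month)).
- Group difference at the 1-month visit: SE ratio = √(mean of the three variances / variance at 1 month).
- Actual type I error = 2·(1 − Φ(1.96 × ratio)).

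**Worked case, SD 8/8/8, r 0.4/0.4/0.8.** D = 2·64·0.6 = 76.8 for each pair with baseline and 2·64·0.2 = 25.6 for the later pair. The mean is 59.7 against a true 76.8. The SE ratio is √(59.7/76.8) = 0.882 and type I error is 8.4%.

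**Worked case, SD 5/9/9.5, r 0.35/0.30/0.80.** D = 74.5, 86.75 and 34.45. The mean is 65.2 against 86.75; the ratio is 0.867 and type I error is 8.9%.

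**Range for the change contrast:**

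| Assumed SDs | Assumed r | SE ratio | Type I error |
|---|---|---|---|
| equal | 0.5/0.5/0.5 | 1.000 | 5.0% |
| equal | 0.5/0.5/0.7 | 0.931 | 6.8% |
| equal | 0.5/0.4/0.8 | 0.850 | 9.6% |
| 5/7/7.5 | 0.6/0.5/0.7 | 0.905 | 7.6% |
| 4.5/9/9.5 | 0.5/0.4/0.8 | 0.866 | 9.0% |
| 4/10/10 | 0.6/0.5/0.7 | 0.946 | 6.4% |
| equal | 0.5/0.6/0.5 | 1.080 | 3.4% |
| 4.5/9/9.5 | 0.5/0.5/0.5 | 1.027 | 4.4% |

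**Sensitivity to the deciding quantity.** Take SD 5/9/9.5 with baseline correlations 0.35 and 0.30, and vary only the post-to-1-month correlation. Type I error is 8.9% at 0.80, 6.5% at 0.60 and 5.6% at 0.50.

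**Smaller baseline SD alone.** With SD 4.5/9/9.5 and all r = 0.5, D = 60.75, 67.75 and 85.75. The mean of 71.4 exceeds 67.75, so the change contrast is slightly conservative (4.4%). With all r = 0.7 it is 5.4%. If inference is instead read as the group difference at the 1-month visit, either case gives √(63.8/90.25) = 0.841, and type I error is 9.9%.

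**Simulation.** REML random-intercept fits (77 per arm, 3,000 runs, Monte Carlo error about 0.5 points) agree. For the change contrast under compound symmetry, type I error was 5.3% with no dropout and 5.5% with 20% random dropout. With SD 4.5/9/9.5 and r 0.5/0.4/0.8 it was 8.6% and 9.7%.

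**The case against.** **The size is assumed.** No SD or correlation appears in the article, and the result turns mainly on how far the post-to-1-month correlation exceeds those with baseline. A reader might infer that the primary test does run at 6-10%. The article does not support that: it shows a structure that its design makes doubtful, not a measured error rate. This objection stands. The cases below 5% for the change contrast are less plausible here: the 3.4% case needs baseline to predict the 1-month score better than post-treatment does, and the 4.4% case needs scores to vary more over the last month (85.75) than from baseline to 1 month (67.75).

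**The entry floor.** Eligibility requires "a total BDD symptom severity score ≥24 on the" BDD-YBOCS-A, which probably narrows the baseline spread. A reader might take this as a second cause of inflation. For the change contrast it is not one by itself, as the working shows; it matters if the contrast is the group difference at the 1-month visit. The article's wording can be read either way, and the two readings can move in opposite directions: with SD 8/6/6 and all r = 0.5 the change contrast runs at 6.3% and the 1-month contrast at 2.8%.

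**The unseen plan.** A random intercept does not exclude a structured residual, and an article may leave that detail to the analysis plan, which prevails. So it cannot be said that the trial will use compound symmetry, only that the article names nothing else.

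**The general remark.** The sentence that mixed models handle within-subject correlation properly describes the method class and is not an error. A random intercept with independent residuals delivers that only under compound symmetry.

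**Conclusion.** The concern holds in conditional form. As the article states it, with independent residuals, the primary model assumes equal variances and equal correlations across visits that differ in spacing, treatment and rater. If the two later visits correlate more strongly with each other than with baseline, at the values assumed above, the model's standard error for the change contrast is about 0.85 to 0.95 of the true one and the nominal 5% test could run at about 6-10%. It is 5% under compound symmetry and can be lower under other patterns. The direction is likely from the design; the size is unknown. The calculations leave out the site terms and treat dropout as random.

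**What to change.** In the primary model, and in the continuous secondary outcomes that share it, keep visit categorical and replace the random intercept with an unstructured 3x3 within-participant covariance, fitted by REML with Kenward-Roger degrees of freedom. Prespecify a fallback for non-convergence, such as a robust standard error. State whether the primary contrast is the change from baseline or the group difference at the 1-month visit. If the full analysis plan already names such a structure, align the article's primary outcome section with it.

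The cost is small: six covariance parameters on about 154 participants, and possibly slightly wider intervals. On complete data the unstructured model uses the variance of the baseline-to-1-month difference itself, which returns the change contrast to its nominal level; if compound symmetry is true, essentially nothing changes. The proposed model with estimated covariance and Kenward-Roger was not itself simulated under dropout.

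Using the same structure in the long-term follow-up model would be consistent, but no error rate was calculated there. The article expects the last primary endpoint in March 2028 and the plan is to be finalised before then, so the change can be made before unblinding.

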#### Long-term follow-up analysis

All trial participants will be naturalistically followed up and assessed up to 6 months after the end of the treatment. Linear mixed-effects models will be implemented for the primary and secondary outcome measures. As for the primary outcome, for each secondary outcome measure, the model will include fixed effects of time (three time points: 1-month follow-up, 3-month follow-up, 6-month follow-up) and site, as well as a time by site interaction, and subject effects as a random intercept factor to account for the variances between and within participants. As above, site will be dropped from the model if its effects are not significant.

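### Keeping or dropping site by significance test leaves the primary 1-month contrast dependent on the outcome data and can cost power if site stays in

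*Protocol article*

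**What the plan says.** Under Primary outcome analysis, the Protocol article specifies a linear mixed model with a random intercept. Its fixed effects are time (three levels), group, site (three levels) and "interaction effects of group by time, group by site, site by time, and group by site by time". The next sentence gives the retention rule: "If the effects of site are not statistically significant, this variable will be dropped from the model to obtain a more parsimonious model". The confirmatory result is the between-group difference at the 1-month follow-up, "estimated from the group by time interaction".

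Under Long-term follow-up analysis the rule returns: "site will be dropped from the model if its effects are not significant". That model has time, site and time by site, but no group term.

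Under Power analysis, the trial is sized as a plain two-group comparison: "we have powered our study to be able to detect at least a moderate effect size of *d* = 0.50", "with a 2-tailed *α* = 0.05", 80% power, 128 evaluable participants and 154 recruited. Nothing is allowed for site-specific treatment effects, and Secondary outcomes analysis says the trial lacks power for moderation of the primary outcome.

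**The concern.** With site dropped, the group by time term at 1 month is the trial-wide difference between ICBT and IRT. With site and all its interactions kept, the same label no longer fixes one quantity. Under reference-cell coding, the raw coefficient is the difference in the reference site alone. Under sum-to-zero coding, or a marginal contrast with equal weights, it is the average of three site-specific differences. The article does not say which applies, and the switch between dropping and keeping is thrown by a significance test on the trial's own outcomes.

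The trigger is also loose. The phrase about effects of site could mean the main effect, any of four terms, or a joint test. Because site is kept or dropped as one variable, clinics that differ only in average severity, with the same treatment effect, could bring the three-way interaction into the confirmatory model. At stake are the meaning of the single primary test and, depending on coding and site sizes, a noticeable share of its power.

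**Working it through.** **Inputs from the article:** d = 0.50, two-sided α = 0.05, 128 evaluable (64 per arm), 1:1 allocation, three sites. **Assumed:** the shares of participants per site, because the article gives none; arms balanced within site; and d taken on the scale of the contrast, so that only relative precision matters.

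**1. The plan's own figure.** Noncentrality = d × √(n per arm / 2) = 0.50 × √(64/2) = 2.83. The two-sample t-test then has 80.1% power, so 128 reproduces (the normal approximation gives 80.7%). The recruitment target also reproduces: 128 × 1.2 = 153.6, rounded up to 154.

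**2. Site kept, reference-cell coefficient.** Only the reference site contributes to the difference. With share s, n per arm = 64s.

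| Reference-site share | n per arm | Noncentrality | Power (t) |
|---|---|---|---|
| 1/3 | 21.3 | 0.50 × √10.67 = 1.63 | 36% |
| 1/2 | 32.0 | 0.50 × √16 = 2.00 | 50% |
| 0.70 | 44.8 | 0.50 × √22.4 = 2.37 | 65% |
| 0.80 | 51.2 | 0.50 × √25.6 = 2.53 | 71% |

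**3. Site kept, equal-weight average of the three site differences.** Variance relative to the pooled contrast = Σ(1/share)/9. Power (normal) = Φ(2.83/√ratio − 1.96).

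| Split | Variance ratio | SE ratio | Power |
|---|---|---|---|
| Equal | (3+3+3)/9 = 1.00 | 1.000 | 81% |
| 50/25/25 | (2+4+4)/9 = 1.11 | 1.054 | 77% (76.5) |
| 60/20/20 | (1.67+5+5)/9 = 1.30 | 1.139 | 70% |
| 70/15/15 | (1.43+6.67+6.67)/9 = 1.64 | 1.281 | 60% |

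Weights proportional to site size give Σ share² × (1/share) = 1, so power returns to about 80%.

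**4. The keep-or-drop rule as a whole.** Simulation with 4,000 runs per scenario, N = 128, complete data, a random-intercept model and within-person correlation 0.5 (assumed). Site is kept if any of its four terms has p < 0.05, which is one reading of the rule.

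| True site effect | Split | Site kept | Overall power, reference-site reading | Overall power, equal-weight reading |
|---|---|---|---|---|
| None | Equal | 19% | 72% | 79% |
| None | 50/25/25 | 19% | 74% | 79% |
| None | 70/15/15 | 19% | 79% | 77% |
| Level only, ±0.4 SD | Equal | 99% | 37% | 80% |
| Level only, ±0.4 SD | 50/25/25 | 96% | 52% | 78% |
| Level only, ±0.4 SD | 70/15/15 | 83% | 68% | 65% |

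These rows are at d = 0.50. With the site terms always left out, power was 79–81%. With no treatment effect, the two-stage procedure rejected in 4.6–5.8% of runs over all scenarios and both readings.

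**The case against.** The strongest reply is that the article does not ask for a reference-site coefficient. It describes the model as estimating a difference between group means and the inference as a between-group difference at the primary endpoint. That reads naturally as a marginal contrast. On that reading, power is 81% for equal sites and about 77% for 50/25/25, close to plan. Coding, weights and test thresholds are also ordinary SAP content, and the Statistical analysis section says the SAP prevails where it differs.

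Much of this stands. A reader might infer that keeping site necessarily turns the result into a one-site effect with most of the power gone. The article does not support that: it follows only from reference-cell coding with the raw coefficient read off, and it weakens when one site dominates. A reader might also infer that choosing the model on the data inflates the false-positive rate; the simulation shows no material inflation. Nor does the argument about the treatment effect carry over to the long-term model, which contains no group term.

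What the reply does not remove is the rule itself. The article states that the primary model will be chosen by a test of site effects, and the full interaction set is written into the starting model. That is a stated choice, not a detail left to the SAP. Even on the favourable reading, uneven sites lose power.

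**Conclusion.** The point holds as a defect of specification. The primary 1-month contrast is conditional on an undefined test of site effects, and a difference in level alone could keep treatment-by-site terms in the confirmatory model of a trial that disclaims power for moderation.

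The size depends on which reading is applied and on site shares that the article does not give. If site is kept, power at 128 evaluable runs from about 36% (reference-site coefficient, one-third share) to about 81% (equal-weight average, equal sites), against the planned 80%. Retention rates rest on the further assumption that any of the four site terms can keep the variable. The consequence is lost power and an unclear estimand, not excess false positives.

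**What to change.** Pre-specify one primary model: group, time, group by time and site, optionally with site by time, all always kept. Delete the rule that removes site when it is not significant. Define the primary result as the overall ICBT–IRT difference at 1 month from that model; without group by site terms the difference is common to all sites, and the coding question disappears. Move group by site and group by site by time to a labelled exploratory analysis of consistency across sites. For consistency, remove the test-based rule from the long-term follow-up model too. Carry the same wording into the SAP, since it prevails.

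The cost is wording, plus 3 − 1 = 2 degrees of freedom for site, or 2 + (3 − 1) × (3 − 1) = 6 with site by time. According to Trial status, recruitment is still open and the last participant is expected to reach the primary endpoint in March 2028, so the change can be made before unblinding.

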### Randomization and allocation concealment

Participants will be randomized at a 1:1 ratio to one of the two interventions (ICBT or IRT) using randomly varying block sizes. Randomization will be conducted using an online randomization service (ALEA Clinical), set up and monitored by an independent clinical trials unit, the Karolinska Trial Alliance (KTA). The research team will not have access to the random allocation sequence. One or several researchers within the team (according to a task delegation list) will be responsible for the enrollment of participants, randomization, and assigning participants to treatments and therapists. Participants will be informed that they will be allocated to one of two psychological treatments for BDD, without providing specific details about the interventions or the study hypotheses.

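### The primary contrast is worded two ways and neither uses the baseline score efficiently; a baseline-adjusted 1-month difference should be named as the estimate

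*Protocol article*

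**What the plan says.** Under Primary outcome analysis, the protocol article specifies a linear mixed model with "fixed effects of time (baseline, post-treatment, and 1-month follow-up), treatment group (ICBT or IRT"), site, all two-way and three-way interactions of group, site and time, and a random intercept. Site is to be dropped if its effects are not significant. The primary outcome is defined as the BDD-YBOCS-A total at 1 month. On the contrast, the section says: "The primary source of inference will be the between-group difference at the primary endpoint (1-month follow-up), estimated from the group by time interaction". It mentions no baseline covariate and no constraint to a common baseline mean.

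The Power analysis section says "we have powered our study to be able to detect at least a moderate effect size of *d* = 0.50" and "A sample size of 128 participants was calculated to be sufficient with a power of 80%, with a 2-tailed *α* = 0.05". It does not say which SD scales d, and it gives no correlation between baseline and endpoint. Under Secondary outcomes analysis, the same modelling framework is carried over to the secondary outcomes.

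**The concern.** When baseline is a level of the time factor and the group effect at baseline is free, the 1-month group by time coefficient is the arm difference at 1 month minus the observed arm difference at baseline. Randomisation makes the true baseline difference zero, so subtracting the observed one in full is efficient only if endpoint tracks baseline with a slope near 1. At lower slopes it adds noise.

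The sentence also describes this quantity as the difference at 1 month, which is a different estimator in any finite sample. Two analysts could follow the text and report different primary results. The sample size appears to rest on a third basis, a plain comparison of endpoint means, so the power of the planned contrast is not tied to the stated 80%.

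**Working it through.** **Inputs from the article.** d = 0.50, two-sided alpha 0.05, power 80%, N = 128 and a 20% addition giving 154 (Power analysis); 1:1 allocation (Randomization and allocation concealment).

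**Inputs not given, so assumed.** r, the correlation of baseline with 1-month score; and k = baseline SD / endpoint SD.

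**Step 1: the plan's own figure.** A two-sample t-test at d = 0.50 needs 63.8 per arm. That rounds to 64, or 128 in total, with power 80.1%. Then 128 × 1.2 = 153.6, giving 154. Both planned figures reproduce with no baseline term.

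**Step 2: variances, with endpoint variance set to 1.**
- Change from baseline: 1 + k² − 2rk.
- Baseline-adjusted: 1 − r².
- Difference between the two: (1 + k² − 2rk) − (1 − r²) = (k − r)².

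The last line is never negative, so in large samples adjustment is never less efficient. The two are equal only when r = k, that is, when the slope of endpoint on baseline (r/k) is 1.

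**Step 3: break-even with the planned power.** The change contrast matches an endpoint comparison when 1 + k² − 2rk = 1, so r = k/2, a slope of 0.5. Below that slope its power is under 80%.

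**Step 4: power at 64 per arm.** The standardised effect is 0.50 / √variance, and power comes from the noncentral t.

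| k | r | Change variance | Change power | Adjusted variance | Adjusted power |
|---|---|---|---|---|---|
| 1 | 0.3 | 1.40 | 66.0% | 0.91 | 83.7% |
| 1 | 0.5 | 1.00 | 80.1% | 0.75 | 90.0% |
| 0.6 | 0.2 | 1.12 | 75.6% | 0.96 | 81.7% |
| 0.6 | 0.3 | 1.00 | 80.1% | 0.91 | 83.7% |
| 0.6 | 0.5 | 0.76 | 89.6% | 0.75 | 90.0% |

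The gain from adjustment in these rows runs from 0.4 points (90.0 − 89.6) to 17.7 points (83.7 − 66.0). At k = 1 and r = 0.2 it is 21.5 points (81.7 − 60.2). At 64 per arm, adjusted power is not below 80% at any r.

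**Step 5: the other reading.** If the sentence means the model-based mean difference at 1 month (group effect plus interaction), power at 64 per arm stays at about 80% whatever r is, provided the random-intercept covariance holds. Baseline then adds essentially nothing to precision.

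**Step 6: check against the planned model.** The table is a two-sample approximation. Simulation (4,000 replicates) of the three-visit random-intercept model with equal SDs and equal correlations gave 67%, 81% and 95% for the interaction test at r = 0.3, 0.5 and 0.7. The change-score formula gives 66.0%, 80.1% and 95.2%.

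**Step 7: does the entry rule matter?** Entry requires a BDD-YBOCS-A score of at least 24. Under a linear relation, truncating baseline lowers r and k together and leaves the slope alone. Starting from a correlation of 0.5 with equal SDs and truncating progressively higher, r fell through 0.45, 0.42, 0.37 and 0.33, while k fell through 0.90, 0.83, 0.75 and 0.66. The ratio r/k stayed at about 0.5 (for example 0.33/0.66) and change-score power at 80.2–80.3%. Adjusted power fell from 88.3% to 84.5%, so truncation narrows the gain.

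**The case against.** A reader might infer that the trial is underpowered, and might point to the entry cut-off as the reason to expect a low correlation. The documents do not support either inference. They state neither r nor any SD, and Step 7 shows that the cut-off does not move the change contrast below its planned power. Baseline and follow-up are rated by different people (site clinicians, then external blinded assessors), which could lower the slope, but nothing in the article says by how much.

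Other points on the plan's side also stand:
- If d = 0.50 was meant on the change-score SD, the 80% holds; the Power analysis section does not say.
- If the sentence means the model-based 1-month difference, the shortfall disappears, though baseline remains unused.
- If all 154 participants are analysed (77 per arm), the change contrast reaches 80% at about r = 0.4 with equal SDs, where 76.3 per arm are needed.
- The table does not describe the planned model when visits are unequally correlated. With equal SDs, r = 0.3 and a correlation of 0.8 between post-treatment and 1 month, the simulated interaction test rejected 74% of the time rather than 66%. Its type I error was then about 9%, so that excess is no real gain in power.
- The separate statistical and health economic analysis plan prevails where it differs from the article, and it may already settle the contrast.

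None of these removes the two findings on the article's text: the contrast is described in two ways, and neither makes efficient use of a baseline score that is already collected.

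**Conclusion.** The point holds as a matter of efficiency and clarity. As written, the primary effect is either a difference in change from baseline or an endpoint difference that leaves baseline unused. Baseline adjustment is at least as precise as both in large samples. Across the assumed values the gain over the change contrast runs from about 0 to about 20 percentage points of power; it is near 0 when the slope approaches 1 and largest when r is low and the SDs are equal.

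A fall below 80% needs r < k/2 with d on the endpoint SD. That is possible but not shown. A reader might also infer that the change contrast is biased; under randomisation it is not, because the expected baseline difference is zero.

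**What to change.** Name the primary estimate as the baseline-adjusted ICBT minus IRT mean difference in BDD-YBOCS-A at 1 month, and estimate it in one of two ways:

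1. Model only the post-treatment and 1-month scores, with baseline score and baseline by visit as covariates.
2. Keep baseline as an outcome visit but constrain the arms to a common baseline mean. This means removing every group term at baseline, both the group main effect and group by site, and keeping group terms only at the post-baseline visits. Removing the group main effect alone does not equalise the baselines while group by site stays in the model.

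Apply the same choice to continuous secondary outcomes that have a baseline measurement. In the Power analysis section, state which SD scales d and what correlation, if any, was assumed.

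The cost is wording and model specification in the protocol and analysis plan, including how the site terms are handled. No new data or change in sample size is needed. The article says the analysis plan will be finalised before the last participant reaches the primary endpoint, expected in March 2028, so the change can still be made before unblinding.
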